### Inclusion criteria

Local authorities comprising the following:Local authorities that commission HENRY and consent for their centres to be involved in the researchCommissioning HENRY programmes delivered by trained staff who have been certified by HENRY

Children’s centres comprising the following:Centres providing routinely collected data for the most recent HENRY programme that they ran at the point of randomisation

### Exclusion criteria

Local authorities:Local authorities which plan to decommission the HENRY intervention during the period of the trial or which are not planning to run any HENRY programmes during the trial period

Children’s centres:Centres which were recruited in the development phase of the optimisation intervention (participating in the rapid ethnography)Centres which are not planning to run any HENRY programmes during the trial period

There will be no exclusions based on the demographics of children’s centres, but location will be monitored to ensure inclusion of those with diverse social and environmental characteristics. Randomisation will also stratify by area-level deprivation to ensure balance between trial arms.

### Recruitment and consent

Local authorities and their centres across the United Kingdom will be identified from an existing database of HENRY delivery sites (see Fig. 2). Those meeting the eligibility criteria will be contacted by invitation letter (postal and electronic) issued jointly by the HENRY central office and the University of Leeds. HENRY is currently commissioned across the whole of the United Kingdom, with most sites situated within England.

**Fig. 2 Fig2:**
[figure not shown]
Recruitment/opt-out process. *HENRY* Health Exercise Nutrition for the Really Young, *LA* Local authorities

Explicit consent will not be sought. Instead, opt-out consent will be sought at the cluster level (local authorities) and from the centres within each local authority. It will be possible for centres to decline participation in the randomisation, even if they are based within a consenting local authority. However, if a local authority declines to take part in the trial, none of its centres will be eligible to take part. Exclusion criteria related to further commissioning of HENRY (local authorities) and plans to run HENRY programmes (centres) will be self-reported by commissioners and centres, respectively. This opt-out method has been chosen because this is a low-risk trial in which anonymised data will be extracted remotely. It has been advocated to promote a simple and efficient trial design, and literature suggests that it is acceptable to participants [45]. It also replicates, as far as possible, the ‘real-life’ conditions under which such quality improvement initiatives are usually conducted in public health. The Leeds Institute of Clinical Trials Research (LICTR) has experience in using an opt-out approach and has found that it (1) is more likely than opt-in methods to provide a more representative or ‘typical’ participating sites; (2) appears more effective and efficient in promoting research participation by sites; and (3) is acceptable, provided that sufficient sensitivity and safeguards are applied [46]. In this instance, individual-/family-level consent is not required, because all patient-level data will be unlinked and anonymous and is routinely collected by centres and submitted to the central HENRY office. Centres will not be asked to conduct any additional data collection from parents for the purposes of this trial. Our parent advisory panel (patient and public involvement group) and trial steering committee (TSC) have both approved this process.

Local authorities and children’s centres will be given 30 days from the date on which the initial information letter is sent to decline participation (confirmed by recorded delivery). Centres that opt out after randomisation will be treated as ‘withdrawn’.

### Unit of randomisation

Local authorities will be randomised in a 1:1 allocation ratio (HENRY + optimisation intervention, HENRY as standard) by a statistician at LICTR, using an algorithm for covariate-constrained randomisation [47] to achieve a balanced allocation between the trial arms on (1) local authority baseline level of parental engagement with HENRY (proportion of centres recruiting a minimum of eight parents per programme, proportion of centres retaining at least 75% of parents for a minimum of five of eight sessions), (2) proportion of centres running at least one HENRY programme in 2015, (3) size of local authorities (number of children’s centres participating), and (4) area deprivation (proportion of centres in the least/most deprived quintiles as ranked by the 2015 Index of Multiple Deprivation at the Lower Layer Super Output Area) [48]. Randomisation will be performed for all local authorities at a single time point after baseline data are transferred, prior to the implementation of the intervention. All possible enumerations of allocation to the trial arms will be generated, and an imbalance statistic will be calculated for each allocation. A set of optimal allocations which minimise the imbalance will be provided, and, in accordance with the principles of International Conference on Harmonisation of Technical Requirements for Registration of Pharmaceuticals for Human Use guidance on randomness, the final allocation will be randomly selected from among this optimal set [49]. Results of the randomisation procedure will be sent by the LICTR statistician to the HENRY central office, which will be responsible for informing local authorities of their treatment allocation.

### Blinding

Owing to the nature of the intervention, it will not be possible to blind allocation within intervention sites or of those involved in the optimisation intervention training. Families attending the HENRY programme have been made aware that HENRY uses data anonymously for research, but they have not been told explicitly about the Optimising Family Engagement in HENRY (OFTEN) trial or whether their local authority has been assigned to the optimisation. HENRY is coordinated by a central team that is responsible for coordinating training and for providing support and QA to areas that commission HENRY. Because the HENRY central office is integral to the delivery of the optimisation intervention, it will not be possible to blind the HENRY central office (as it will communicate the randomisation allocation to all those responsible for its implementation); however, staff who are responsible for collating data and transferring it to LICTR will remain blinded to allocation. The chief executive officer of HENRY will be blinded to treatment allocation and will not attend TSC meetings. In addition, for the duration of the trial, the HENRY QA team have agreed to reallocated areas that they are responsible for, so that only one person will have contact with areas allocated to the optimisation intervention. Other QA staff will be aware that they have standard QA responsibility (e.g., answering questions, providing encouragement, checking on progress) for areas not randomised to the optimisation, but will not know the details or content of the optimisation intervention. To further avoid contamination, the details of the optimisation intervention will not be published until after the final analysis. Unplanned masking (unblinding) will be monitored and reported to the TSC.

### Intervention

#### HENRY

HENRY is an 8-week programme delivered in children’s centres with the aim of providing parents with skills, knowledge and confidence to support healthy lifestyles among their preschool children and their families, including parenting skills, emotional well-being and activity. The programme was set up in 2006 with the aim of reversing rising trends in school entry age obesity. HENRY is currently delivered within 32 local authorities across England and Wales by trained health and community practitioners who undergo two stages of training [26]. Stage 1, centre-level training, is a 2-day workshop designed to equip centre staff with knowledge and skills to promote and provide healthy nutrition within early years settings and support parents to provide healthy family lifestyles and nutrition for their families. The theoretical underpinning combines proven models of behaviour change, including the Family Partnership Model, motivational interviewing and solution-focused support. Stage 2, practitioner-level training to deliver the HENRY programme to families, is provided to approximately four practitioners per centre after completing Stage 1 to deliver the 8-week HENRY programme. The aim of this stage is to build parents’ skills, knowledge and confidence to change old habits, provide healthier nutrition for their young children, and encourage healthier lifestyles [25, 27]. Programme content includes sessions on lifestyle and eating habits (e.g., family meals), balancing healthy meals and snacks, child-appropriate portion sizes, parenting, physical activity and emotional well-being.

Current HENRY QA practice involves the review of process data by dedicated individuals in the HENRY central office with provision of written and oral feedback. This QA will continue in both trial arms and will be monitored. Staff delivering current QA activities will be blinded to treatment allocation.

#### HENRY + parent engagement optimisation intervention

We summarise only the key features of the optimisation intervention in the trial protocol to minimise contamination (i.e., uptake of initiatives of the intervention by local authorities randomised to the control arm) and maintain blinding. The optimisation intervention consists of interacting components delivered to local authorities, children’s centres and HENRY facilitators. It includes additional support to stakeholders, modification of HENRY marketing to clarify perceptions of the programme, and methods to modify the pre-programme experience for parents. Strategies have been developed to increase parent motivation to enrol in HENRY and promote parent self-efficacy to continue to attend. Implementation of the optimisation intervention will begin immediately following randomisation. All components of the optimisation intervention will be implemented within 6 months following randomisation.

#### HENRY as standard

Local authorities randomised to the control arm will continue to deliver HENRY programmes as per standard practice.

### Outcomes

#### Primary outcome

The effectiveness of the optimisation intervention will be determined by comparing parent engagement in HENRY + optimisation intervention vs HENRY alone. The co-primary outcomes are (1) the proportion of centres enrolling at least eight parents per programme and (2) the proportion of centres with at least 75% of parents attending five of eight sessions per programme. Both will be evaluated 12 months post-randomisation. The optimisation intervention will be deemed effective if either the enrolment or attrition goals are met.

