### Sample size

We assumed that 25% of the 32 local authorities currently running HENRY will not be eligible or will opt out of the study, leaving 24 local authorities (12 per arm). Power calculations for this fixed sample size (with all eligible centres in the United Kingdom invited to take part) were therefore conducted to examine anticipated power for various intervention effects, at the 5% significance level, in each of the primary outcomes and for the composite endpoint (enrol at least eight parents per programme and retain ≥75% of parents attending five of eight sessions) (see Table 1 for scenarios). On the basis of data from previous HENRY programmes (all terms in 2014), we assumed an average of 6 children’s centres per local authority providing a total of 144 children’s centres (72 per arm), an intra-cluster correlation coefficient (ICC) between 0.05 and 0.1, a coefficient of variation in cluster size of 0.54, and the following estimates of the outcomes in the control sites (HENRY alone): 55% of centres will enrol at least eight parents per programme; 50% of centres will retain ≥75% of parents attending five of eight sessions; and 25% of centres will enrol at least eight parents per programme and retain ≥75% of parents attending five of eight sessions. Thus, with the anticipated number of centres (24 local authorities, 144 children’s centres), we will have at least 80% power to detect meaningful improvements in differences of between 25% and 30% in either of the primary endpoints or the composite endpoint at the 5% significance level, assuming the ICC is no greater than 0.05.

**Table 1 Tab1:** Power calculations for enrolment and attrition endpoints for various estimates of the intervention effect and a fixed sample size of 144 children’s centres in 24 local authorities

Outcome in the control	Percentage point increase in intervention	Power for ICC = 0.1	Power for ICC = 0.05
Enrolment (≥8 parents per programme)			
55%	5%	6%	7%
	10%	15%	18%
	15%	29%	35%
	20%	49%	58%
	25%	70%	79%
	30%	87%	93%
Attrition (≥75% of parents attending five of eight sessions)			
50%	5%	6%	7%
	10%	15%	17%
	15%	28%	34%
	20%	47%	55%
	25%	67%	76%
	30%	84%	91%
Enrolment and attrition (at least eight parents per programme and 75% of parents attending five of eight sessions)			
25%	5%	7%	8%
	10%	17%	19%
	15%	31%	37%
	20%	49%	58%
	25%	67%	76%
	30%	82%	89%

*ICC* Intra-cluster correlation coefficient

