### Analysis

Statistical analysis of the quantitative elements of the trial is the responsibility of the LICTR statisticians. The analysis plan outlined in this section will be reviewed, and a detailed statistical analysis plan will be written and approved, before any formal analyses are undertaken. Statistical analyses will be carried out by the ITT principle, and statistical significance will be assessed at the two-sided 5% significance level. The ITT population is defined as analysis according to the randomisation and regardless of compliance with the protocol or withdrawal from the trial.

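### Either co-primary outcome can declare the intervention effective and each is tested at a full two-sided 5%, so the family-wise error is about 9.7%, not 5%

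*Protocol article*

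**What the plan says.** The Primary outcome section sets two outcomes and one verdict. "The co-primary outcomes are (1) the proportion of centres enrolling at least eight parents per programme", and the second is the proportion of centres in which at least 75% of parents attend five of the eight sessions. The verdict is a union: "The optimisation intervention will be deemed effective if either the enrolment or attrition goals are met". The first primary objective uses the same 'or' between enrolment and attrition.

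The Analysis section says that "statistical significance will be assessed at the two-sided 5% significance level". The Sample size section states that power was examined "at the 5% significance level, in each of the primary outcomes and for the composite endpoint". It then claims at least 80% power for differences of 25 to 30 points "in either of the primary endpoints or the composite endpoint at the 5% significance level, assuming the ICC is no greater than 0.05".

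The Primary analysis section describes a weighted t test of cluster-level proportions for both outcomes. It gives no alpha split, testing order, step-down procedure or joint test, and none appears elsewhere in the article.

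**The concern.** Two chances to win at 5% each do not give one verdict at 5%. Calling the outcomes 'co-primary' does not help. Unadjusted testing controls the error only when both outcomes must succeed, and here one is enough.

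What is at stake is the trial's main conclusion, that the optimisation is effective. As written, that statement carries close to twice the error rate a reader would take from the Analysis section. The power figures have the matching fault, because they were obtained at a level that a properly controlled either/or rule cannot give to each outcome.

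**Working it through.** **Inputs** (Sample size, Primary outcome and Analysis sections)
- 24 local authorities, 12 per arm; 144 centres, 72 per arm; mean cluster size 6.
- "an intra-cluster correlation coefficient (ICC) between 0.05 and 0.1, a coefficient of variation in cluster size of 0.54".
- Control rates: enrolment 55%, attrition target 50%, both together 25%.
- Two-sided 5%; success if either outcome wins.

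**1. Reproduce Table 1, to see which alpha it uses**

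Design effect = 1 + ((1 + CV²) × 6 − 1) × ICC, with CV² = 0.2916.
- ICC 0.05: 1.337, so effective n per arm = 72/1.337 = 53.8.
- ICC 0.10: 1.675, so effective n per arm = 72/1.675 = 43.0.

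A two-proportion normal approximation (pooled variance under the null, no continuity correction) on these effective sizes gives, at ICC 0.05:

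| Comparison | Table 1 | alpha 5% | alpha 2.5% |
|---|---|---|---|
| Enrolment 55% v 80% | 79% | 79.9% | 70.8% |
| Enrolment 55% v 85% | 93% | 93.6% | 88.9% |
| Attrition 50% v 75% | 76% | 77.2% | 67.5% |
| Attrition 50% v 80% | 91% | 91.5% | 85.9% |

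At 5%, all 36 cells of the table agree within 1.4 points. At 2.5% the same formula misses by up to 11 points. A noncentral t with 22 degrees of freedom also fits within 1.4 points at 5%. Table 1 therefore uses an unsplit 5% for each outcome.

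**2. Correlation implied by the planning rates**

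The protocol assumes that "25% of centres will enrol at least eight parents per programme and retain ≥75% of parents attending five of eight sessions" in the control sites. Independence would give 0.55 × 0.50 = 0.275, so

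phi = (0.25 − 0.275) / √(0.55 × 0.45 × 0.50 × 0.50) = −0.025 / 0.2487 = −0.10.

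**3. Error rate with no effect on either outcome**

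Under independence:
- Any two-sided p < 0.05: 1 − 0.95² = 9.75%.
- Any significant result in favour of the intervention: 1 − 0.975² = 4.94%, against 2.5%.

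Under a bivariate normal with other correlations:

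| Correlation | At least one p < 0.05 | At least one false claim of benefit |
|---|---|---|
| −0.3 | 9.5% | 5.0% |
| −0.10 | 9.7% | 5.0% |
| 0 | 9.75% | 4.9% |
| 0.3 | 9.5% | 4.8% |
| 0.5 | 9.1% | 4.5% |
| 0.8 | 7.8% | 3.9% |

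Simulating two t tests on 12 v 12 clusters gives the same picture: 9.7% to 9.8% near zero correlation, about 9.0% at 0.5 and 7.9% at 0.8.

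**4. With the error controlled**

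With the smaller p-value tested at 2.5%, the family-wise error near zero correlation is 1 − 0.975² = 4.9%. Power by the noncentral t with 22 df, enrolment / attrition:

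| Difference | ICC | alpha 5% | alpha 2.5% |
|---|---|---|---|
| 25 points | 0.05 | 78.4% / 75.5% | 68.0% / 64.5% |
| 30 points | 0.05 | 93.0% / 90.7% | 87.4% / 84.0% |
| 25 points | 0.10 | 68.9% / 65.9% | 57.1% / 53.8% |
| 30 points | 0.10 | 86.6% / 83.5% | 78.4% / 74.3% |

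If both outcomes truly improve by 25 points and are independent, the chance of winning at least one is:
- ICC 0.05: 1 − (1 − 0.680)(1 − 0.645) = 89%.
- ICC 0.10: 1 − (1 − 0.571)(1 − 0.538) = 80%.

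**The case against.** - **The analysis plan may deal with it.** The article says a detailed plan will follow, and alpha allocation is often settled there. But the article does not leave the matter open: it states the decision rule, the level, and power at that level for each outcome. A plan that split alpha would depart from the Sample size section and make Table 1 wrong. Whether the unseen plan adjusts is unknown; the point is about what the article fixes.
- **Meeting a 'goal' is not defined as p < 0.05.** This is true and is a real qualification. However, the Primary outcome section says effectiveness is judged by comparing the arms, and the 5% level is the only criterion given for that comparison.
- **Only a favourable result would be called effective, so 9.7% overstates false success.** This is fair. The 9.7% is the two-sided family-wise rate, to be set against the stated two-sided 5%. A false claim of benefit has a chance of about 4.9% to 5.0%, to be set against 2.5%. Both comparisons show about a doubling.
- **The correlation is weakly supported.** The planning rates look rounded. If each is taken as rounded to the nearest 5 points (an assumption), phi could lie between about −0.31 and +0.10. It is also a centre-level figure, whereas the test uses local-authority proportions. The sign is therefore not established. Across that range the two-sided error stays between about 9.5% and 9.75%, and any correlation short of 1 leaves some inflation.
- **Little hangs on the verdict.** Willingness to pay is elicited separately, and the Discussion says the follow-on pilot will go ahead whatever this trial shows. This limits the practical consequences, but the statement of effectiveness still carries an error rate the protocol does not declare.

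**Conclusion.** The plan is wrong as written. An either/or success rule with an unsplit two-sided 5% on each outcome gives a family-wise error of about 9.7% instead of 5%, and a false-benefit rate of about 4.9% to 5.0% instead of 2.5%.

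These figures assume no true effect on either outcome, that meeting a goal means statistical significance at the stated level, and a correlation near zero between the two cluster-level comparisons, as the planning rates suggest. A correlation of 0.8 would bring the two-sided figure down to about 8%, still well above 5%.

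**What to change.** Keep the either/or rule and test the two outcomes by Holm's procedure at an overall two-sided 5%: the smaller p-value against 2.5% and, if that succeeds, the other against 5%. Holm holds under any dependence, so the uncertain correlation does not matter. Other valid methods exist, but Holm is simple and never weaker than a fixed 2.5% split. State it in the Primary outcome section, the Analysis section and the analysis plan, and say there that a goal is met when the outcome is significant in favour of the intervention under that procedure.

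Restate Table 1 for the two co-primary outcomes at 2.5%, and revise the power claim. At an ICC of 0.05, 80% power per outcome would still hold at 30 points (87% and 84%) but not at 25 points (68% and 65%). The chance of at least one success can be reported beside these figures, with its independence assumption stated.

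The cost is wording and a revised table, plus about 10 points of per-outcome power at 25 points. Design, sample and data collection do not change. The article says the analysis plan will be approved before any formal analysis, so the change can be pre-specified there.

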#### Secondary outcomes

Secondary outcomes, measured 12 months post-randomisation (unless stated otherwise), include some further assessment of parent engagement to explore the degree to which the intervention was effective. Data from additional questionnaires which are routinely administered by HENRY facilitators at the beginning and end of each 8-week course will also been analysed to explore the potential impact of the optimisation on behavioural outcomes, outlined below:Proportion of centres achieving all targets for enrolment, attrition and parent complianceParent adherence to HENRY programme content, defined as the proportion of parents reporting an increase of 0.5 in the daily frequency of consumption of fruits and vegetables by children per programmeImpact of HENRY on parenting and family health, assessed by parent-report, including the following:
*Parenting self-efficacy* (assessed via four parenting confidence items with 5-point Likert scales, modified from the validated Parenting Self-Agency Measure [50]). This measure assesses the parents’ estimate of their ability to influence their child and environment to lead to positive development, which is a key goal of the HENRY approach. In order for the questionnaire to be feasible to administer as part of the service, HENRY chose to reduce the number of items to a single scale of parenting confidence. Internal consistency of these items in a previous HENRY evaluation was high, and internal consistency in this sample was high (Cronbach’s alpha = 0.82 at baseline, 0.74 at completion) [51].
*Eating behaviours* (based on the Golan Family Eating and Activity Habits Questionnaire [52]). This validated measure is sensitive to change and demonstrates high levels of reliability and validity. HENRY facilitators routinely administer six items related to family behaviours, included parent report of family sitting together for meals, watching television during mealtimes, consuming take-out meals, consumption of home-cooked foods, stopping eating when full and choosing healthy meals. Individual evaluation of these items will be undertaken because reliability for the scale was poor when previously tested using HENRY families (Cronbach’s alpha = 0.52 at baseline, 0.56 at completion).
*Family activity* (via a brief HENRY questionnaire asking parents to report the frequency that parents and children engage in exercise). This questionnaire has been developed bespoke to use within the HENRY evaluations and includes parental report of their own activities that result in breathlessness, with response categories ranging from none to <1 h, 2 h, 3 h or >3 h. Children’s activity is assessed using parental report as energetic play, with response categories ranging from none to 5–15 minutes, 20–30 minutes, 30 minutes to 1 h, or >1 h.
*Child screen time* (via a parent reported using the bespoke HENRY questionnaire). This assesses use of televisions, DVDs, computers, smartphones, and so forth with response categories ranging from none to <1 h, 1–2 h, 2–3 h, or >3 h.
*Intake of key indicator foods per day* (assessed via 14 items from a modified validated Food Frequency Questionnaire [53] completed in relation to the parent and child). Parents are asked to estimate how often (never, once per month, once per fortnight, 1–7 days per week) they consumed each of the 14 items or groups of foods (e.g., fresh fruit, sweets, chocolate, water), with space to report the number of times consumed. It has previously demonstrated sensitivity to change with parents attending HENRY sessions [25].
Longitudinal impact of HENRY + optimisation intervention vs HENRY alone (parent engagement [enrolment and attrition] within centres during the 12-month follow-up in local authorities which provide data for more than one programme per centre at follow-up) (This evaluation will explore whether the optimisation intervention needs time to ‘bed-in’ and/or whether any early effects are maintained over time.)

